#### Primary outcome

The primary outcomes are average weekly back pain intensity (trial one) and
average weekly knee pain intensity (trial two), measured over the course of
follow up.

Participants were asked to report the “average pain intensity experienced in
their back (trial one) or knee (trial two) over the past week, on a 0 to 10
NRS, where 0 was ‘no pain’ and 10 was the ‘worst possible pain’”^6^. These pain intensity scores were measured at baseline, at 2, 6, 10,
14, 18, 22 and 26 weeks. Average weekly (back or knee) pain intensity is
defined as the Area under the Curve (AUC) of the pain intensity trajectory,
over the follow up period. The AUC for each participant will be computed
using the trapezoid rule.

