#### Data collection and follow up

The different stages of data collection and follow-up for secondary outcomes
are summarised in table one. The primary outcome, pain intensity score, was
collected at baseline, week 2, 6, 10, 14, 18, 22 and at 26 weeks. Baseline
assessment was conducted prior to randomisation.

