### Methods for handling missing data

The number of participants with missing observations will be reported for each
outcome variable. Patterns of missing data will be investigated and compared by
demographic characteristics of the participants, t-tests will be used to compare
continuous variables and chi-square tests will be used to compare categorical
variables. For the primary outcome variable (average weekly pain intensity
score) for participants with <10% missing pain intensity values, the missing
pain intensity values will be interpolated using cubic spline interpolation. For
participants with 10% or greater missing data an AUC will not be computed. The
primary method of dealing with missing AUC data will be through multiple
imputation (assuming missing at random), where missing AUC data will be imputed
using the chained equations method of generating a number of complete data sets;
the imputation model will include a range of covariates believed to be
associated with either the missing outcome or the outcome itself (baseline pain
and duration, waiting time, BMI). Sensitivity of analysis results will be
assessed by comparing results obtained various imputation models. If there is
reason to suggest the data may be missing not at random, pattern mixture models
will be utilised^24^.

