### Primary analysis

To examine between-group differences in the primary outcome (AUC – based on pain
intensity score) we will use an independent sample Students t-test. The primary
analysis will not adjust for known prognostic variables as covariates, but
results adjusting for these will be presented as a sensitivity analysis (see
below). Separate models will be estimated for each imputed dataset and the means
and standard errors will be combined using Rubin’s method^25^. We will assess other model assumptions (homoscedasticity, normality)
through inspecting appropriate residual plots, where serious violations are
observed we will apply a rank-inverse normal transformation to the pain
intensity score values. Dummy coded variables representing group allocation will
be used to ensure blinding of the analyses. See Table 3 for details.

**Table 3 t03:** Analyses of primary outcome.

**Analysis**	**Outcome**	**Intervention**	**Control**	**Difference**
Primary (ITT Multiple Imputation)	Area under the pain intensity curve (AUC)	mean(95%CI)	mean(95%CI)	mean(95%CI)
Sensitivity	Adjusted AUC*	mean(95%CI)	mean(95%CI)	mean(95%CI)
Secondary	Pain intensity score			
	Baseline	mean(SD)	mean(SD)	
	Week 2,	mean(SD)	mean(SD)	
	Week 6	mean(SD)	mean(SD)	
	Week 10	mean(SD)	mean(SD)	
	Week 14	mean(SD)	mean(SD)	
	Week 18	mean(SD)	mean(SD)	
	Week 22	mean(SD)	mean(SD)	
	Week 26	mean(SD)	mean(SD)	
	Weekly trend	mean(95%CI)	mean(95%CI)	mean(95%CI)

* Adjusted for baseline pain and duration, waiting time, previous
surgery; BMI: physical activity and dietary intake; ITT: Intention
to treat.

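### If the residual plots look seriously wrong, the plan moves the primary result to a rank-normal scale that cannot be read in NRS points

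*Protocol article*

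**What the plan says.** Under Primary outcome, the protocol article asks for pain on a 0 to 10 NRS. Average weekly pain intensity is "defined as the Area under the Curve (AUC) of the pain intensity trajectory", computed by the trapezoid rule. Data collection and follow up says the scores are "collected at baseline, week 2, 6, 10, 14, 18, 22 and at 26 weeks", so there are eight per participant.

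Under Primary analysis, the AUC is compared by an unadjusted Student's t-test in each imputed dataset, and the results are pooled by Rubin's method. Homoscedasticity and normality are judged from residual plots, and "where serious violations are observed we will apply a rank-inverse normal transformation to the pain intensity score values". No numeric threshold and no back-transformation are given. Table 3, in the same section, gives the primary result as a mean AUC difference with 95% CI.

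Under Methods for handling missing data, a participant with 10% or more of scores missing gets no computed AUC, and "missing AUC data will be imputed" by chained equations. Under Sample size, the trials are sized on differences of 1.5 (trial one) and 2 (trial two) NRS points.

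**The concern.** The fallback changes the scale of the primary estimate after the outcome data have been examined. A rank-inverse normal transformation replaces each value by a normal quantile of its rank. A difference between groups is then counted in normal-score units, whose meaning depends on how spread out the sample is. The primary objective concerns improvement in pain intensity, and the design rests on differences in NRS points described as clinically meaningful. The transformed result cannot be compared with them.

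Nothing ties the decision in one trial to the decision in the other, so the rule could fire in one only. The two primary results would then not be on a common scale.

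A second difficulty arises if the wording means the visit scores. The residuals being checked belong to the AUC comparison, and the AUC is what is imputed, but the remedy would act on a different variable.

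**Working it through.** **1. Which variable is transformed.** Primary analysis describes the AUC as based on the pain intensity score, and Table 3 lists the visit scores under that name in rows separate from the AUC. The plain reading is therefore the visit scores. However, Methods for handling missing data calls the primary outcome variable the average weekly pain intensity score, which Primary outcome defines as the AUC. Both readings are checked below.

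**2. Scale before transformation.** Suppose the groups are equal at baseline and differ by 1.5 points from week 2 on. The trapezoid AUC difference is 1.5 × 2/2 + 1.5 × 24 = 37.5 NRS-weeks. Divided by 26 weeks this is 1.44 points. The article does not state this division, but it is a known constant, so the untransformed result can always be set against 1.5 or 2 points.

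**3. Scale after transformation.** The simulation used 80 per arm, eight scores rounded and clipped to 0–10, a 1.5-point shift at all follow-up visits and 300 replicates. Assumed, not from the article: control mean 5.5, within-person SD 1.3, between-person SD 1.0, 1.9 or 2.5. The time-averaged AUC differences were:

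| Between-person SD | Untransformed (NRS points) | Scores ranked within visit | Scores ranked over all visits | AUC itself ranked |
|---|---|---|---|---|
| 1.0 | 1.44 | 0.76 | 0.77 | 1.07 |
| 1.9 | 1.41 | 0.58 | 0.58 | 0.69 |
| 2.5 | 1.32 | 0.46 | 0.47 | 0.53 |

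The last three columns are in normal-score units. For within-visit ranking, NRS points per normal-score unit are 1.436/0.760 = 1.89, 1.410/0.575 = 2.45 and 1.317/0.464 = 2.84. There is no fixed conversion factor. Ranking the AUC itself loses the scale in the same way.

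**4. Fit with the imputation (visit-score reading only).** One missing score is 1/8 = 12.5% of all scores, or 1/7 = 14.3% of follow-up scores. Both exceed 10%, so every participant with any missing score has an AUC imputed as a single number. If scores are missing independently with probability p at each of seven follow-up visits (assumed), the share affected is 1 − (1 − p)^7: 13% for p = 2%, 30% for p = 5% and 52% for p = 10%. Transforming visit scores leaves an AUC already imputed unchanged. To reach these participants, the observed scores must be transformed first, the AUCs recomputed and the imputation rerun.

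**5. Whether the t-test needs the remedy.** Both checks used 20,000 null simulations per setting at nominal 0.025. The Monte Carlo standard error is √(0.025 × 0.975/20,000) = 0.0011.
- Eight rounded, truncated scores (correlation 0.6 assumed, SD 2.7), 51 per arm (0.85 × 60), AUC skewness 0.00, 0.45, 0.72 and 1.07: rejection rates 0.0250, 0.0239, 0.0259 and 0.0242.
- A skewed bounded outcome (10 × beta(1.2, 4), assumed): 0.026 with 51 per arm and 0.025 with 68 per arm (0.85 × 80).

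The t-test held its size in every setting. Neither check included unequal variances, multiple imputation or power.

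**The case against.** The best defence is that the fallback is pre-specified, is reserved for serious violations, and is applied by an independent statistician who is blinded to group and works with dummy-coded allocation. That stands, and it answers most of any suspicion that the switch could be used to favour a result. It does not restore the NRS scale.

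A reader might infer that the rule cannot be carried out on imputed data at all. The article does not support that. Scores can be transformed before the AUCs are computed and the imputation then rerun, and if the AUC is the variable meant, it can be transformed within each imputed dataset. The order of steps may also be given in the signed analysis plan, which is not shown. What stands is narrower: as worded, the rule does not match AUC-level imputation.

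A reader might also infer that the trials could no longer say whether pain fell by a meaningful amount. That goes too far. Table 3 also reports visit means by group and a difference in weekly trend, nothing extends the transformation to those rows, and nothing forbids showing the untransformed AUC as well. But these would not be the designated primary result.

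Finally, rank-normalisation is a recognised technique and may gain efficiency with strongly skewed data. The simulations examined type I error only, so they do not refute this.

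**Conclusion.** The point holds as a flaw in a conditional rule. If the fallback is triggered, the primary difference in that trial is in normal-score units on either reading of the wording. It then cannot serve as the mean AUC difference that Table 3 promises or be judged against 1.5 or 2 NRS points. This follows from the text and needs no simulation. The simulated values (0.46 to 1.07 units for the same 1.5-point shift, over both readings) only illustrate the loss and depend on the assumed SDs. The mismatch with the imputation holds only if visit scores are meant, and the share of participants affected depends on the assumed missingness.

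It would be too strong to say that the transformation has been shown to be unnecessary. Type I error of about 0.024–0.026 at nominal 0.025 supports keeping the t-test scale, but it rests on assumed distributions, equal variances and no imputation. The change is worth making because it costs little and protects how the primary result is read.

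**What to change.** Keep the primary estimate as the untransformed AUC difference in both trials, divided by 26 so that it reads in NRS points. Use a Welch or heteroscedasticity-robust standard error from the start, which deals with unequal variances directly, and pool by Rubin's method as planned. If residuals are badly non-normal, add a bootstrap interval on the same scale. Keep the rank-inverse normal analysis as a sensitivity analysis only. State whether it transforms visit scores or the AUC and, if visit scores, whether ranking is within visit or over all visits. State also whether the transformation comes before imputation.

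The cost is a sentence or two in the plan and a little more analysis work, including a decision on how the bootstrap and the imputation are combined. Some efficiency may be lost if the AUC is strongly skewed. The sensitivity analysis would show whether that matters.

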### Secondary analysis

Between group differences in the trajectory of pain intensities over the
follow-up period will be examined using growth curve modelling. Hierarchical
linear models will be used, with fixed effects for treatment group, time, and
the interaction between the two. The model will include random subject-level
intercepts and slopes. A linear growth trend will initially be assumed, and if
not appropriate different functional forms for the trend will be applied (for
example the square root transformation). If an appropriate functional form
cannot be determined a flexible piecewise linear model will be used^26^. We will also investigate treatment effect heterogeneity that may exist
in latent subgroups of participants through growth mixture models^27^. In these models a number of latent classes are specified that model the
potential for participants to have different trajectory types, the functional
forms identified from the previous growth curve analyses will inform the
functional forms for this analysis. The model will include the following random
effects that are all conditional trajectory class membership: intercept linear
slope and quadratic slope. The random effects are influenced by the treatment
group, so there will potentially be 3 lots of treatment effects (for each random
effect) for each latent class.

Longitudinal generalised linear mixed models will be used to assess treatment
effect on post randomisation secondary outcome measurements with random
intercepts for individuals to account for correlation of repeated measures and
an appropriate link function dependent on the type and distribution of the data.
We will compare the adjusted mean change (continuous variables) or relative
risks (dichotomous variables) in outcome from baseline to each time point
between the treatment and control groups. A binomial distribution family (with
log link) will be used for dichotomous outcomes (sleep quality, smoking
prevalence), and a Poisson or negative-binomial distribution family (with a log
link function) will be used for count outcomes (health care utilisation) based
on assessment of data dispersion. T-tests will be used to test between group
differences in variables collected only at 26 weeks (objective weight, BMI,
waist circumference). See Table 4 for
details.

**Table 4 t04:** Secondary outcomes.

**Outcome**	**Intervention**	**Control**	**Intervention - control**
Disability and function (Trial 1: RMDQ / Trial 2: WOMAC)			
Baseline	mean (SD)	mean (SD)	mean (95% CI)
Week 6	mean (SD)	mean (SD)	mean (95% CI)
Week 26	mean (SD)	mean (SD)	mean (95% CI)
Overall	mean (SD)	mean (SD)	mean (95% CI)
Subjective weight			
Baseline	mean (SD)	mean (SD)	mean (95% CI)
Week 6	mean (SD)	mean (SD)	mean (95% CI)
Week 26	mean (SD)	mean (SD)	mean (95% CI)
Overall	mean (SD)	mean (SD)	mean (95% CI)
Objective weight			
Baseline^a^	mean (SD)	N/A	N/A
Week 26	mean (SD)	mean (SD)	mean (95% CI)
BMI			
Baseline	mean (SD)	mean (SD)	mean (95% CI)
Week 6	mean (SD)	mean (SD)	mean (95% CI)
Week 26	mean (SD)	mean (SD)	mean (95% CI)
Overall	mean (SD)	mean (SD)	mean (95% CI)
Waist circumference			
Week 26	mean (SD)	mean (SD)	mean (95% CI)
Quality of life (SF12v2, PCS)			
Baseline	mean (SD)	mean (SD)	mean (95% CI)
Week 6	mean (SD)	mean (SD)	mean (95% CI)
Week 26	mean (SD)	mean (SD)	mean (95% CI)
Overall	mean (SD)	mean (SD)	mean (95% CI)
Quality of life (SF12v2, MCS)			
Baseline	mean (SD)	mean (SD)	mean (95% CI)
Week 6	mean (SD)	mean (SD)	mean (95% CI)
Week 26	mean (SD)	mean (SD)	mean (95% CI)
Overall	mean (SD)	mean (SD)	mean (95% CI)
Perceived change in condition (GPE)			
Week 6	mean (SD)	mean (SD)	mean (95% CI)
Week 26	mean (SD)	mean (SD)	mean (95% CI)
Overall	mean (SD)	mean (SD)	mean (95% CI)
Emotional distress (DASS-21)			
Baseline	mean (SD)	mean (SD)	mean (95% CI)
Week 26	mean (SD)	mean (SD)	mean (95% CI)
Overall	mean (SD)	mean (SD)	mean (95% CI)
Poor sleep quality (item 6, Pittsburgh Sleep Quality Index)			
Baseline	n/N (%)	n/N (%)	OR (95% CI)
Week 6	n/N (%)	n/N (%)	OR (95% CI)
Week 26	n/N (%)	n/N (%)	OR (95% CI)
Overall	n/N (%)	n/N (%)	OR (95% CI)
Physical activity (mins MVPA/week)			
Baseline	mean (SD)	mean (SD)	mean (95% CI)
Week 6	mean (SD)	mean (SD)	mean (95% CI)
Week 26	mean (SD)	mean (SD)	mean (95% CI)
Overall	mean (SD)	mean (SD)	mean (95% CI)
Diet (Fruit, serves)			
Baseline	n/N (%)	n/N (%)	OR (95% CI)
Week 6	n/N (%)	n/N (%)	OR (95% CI)
Week 26	n/N (%)	n/N (%)	OR (95% CI)
Overall	n/N (%)	n/N (%)	OR (95% CI)
Diet (Vegetable, serves)			
Baseline	n/N (%)	n/N (%)	OR (95% CI)
Week 6	n/N (%)	n/N (%)	OR (95% CI)
Week 26	n/N (%)	n/N (%)	OR (95% CI)
Overall	n/N (%)	n/N (%)	OR (95% CI)
Diet (Discretionary foods, serves)			
Baseline	n/N (%)	n/N (%)	OR (95% CI)
Week 6	n/N (%)	n/N (%)	OR (95% CI)
Week 26	n/N (%)	n/N (%)	OR (95% CI)
Overall	n/N (%)	n/N (%)	OR (95% CI)
Alcohol consumption (AUDIT)			
Baseline	mean (SD)	mean (SD)	mean (95% CI)
Week 6	mean (SD)	mean (SD)	mean (95% CI)
Week 26	mean (SD)	mean (SD)	mean (95% CI)
Overall	mean (SD)	mean (SD)	mean (95% CI)
Smoking prevalence			
Baseline	n/N (%)	n/N (%)	OR (95% CI)
Week 6	n/N (%)	n/N (%)	OR (95% CI)
Week 26	n/N (%)	n/N (%)	OR (95% CI)
Overall	n/N (%)	n/N (%)	OR (95% CI)
Pain Attitudes (SOPA)			
Baseline	mean (SD)	mean (SD)	mean (95% CI)
Week 6	mean (SD)	mean (SD)	mean (95% CI)
Week 26	mean (SD)	mean (SD)	mean (95% CI)
Overall	mean (SD)	mean (SD)	mean (95% CI)
Fear avoidance beliefs (FABQ)			
Baseline	mean (SD)	mean (SD)	mean (95% CI)
Week 26	mean (SD)	mean (SD)	mean (95% CI)
Overall	mean (SD)	mean (SD)	mean (95% CI)
Health care utilisation (Medication use for back or knee pain)			
Baseline	n/N (%)	n/N (%)	OR (95% CI)
Week 6	n/N (%)	n/N (%)	OR (95% CI)
Week 26	n/N (%)	n/N (%)	OR (95% CI)
Overall	n/N (%)	n/N (%)	OR (95% CI)
Health care utilisation (Visits for back or knee pain)			
Baseline	n/N (%)	n/N (%)	OR (95% CI)
Week 6	n/N (%)	n/N (%)	OR (95% CI)
Week 26	n/N (%)	n/N (%)	OR (95% CI)
Overall	n/N (%)	n/N (%)	OR (95% CI)
Health care utilisation (Attended orthopaedic consultation for back or knee)			
Week 26	n/N (%)	n/N (%)	OR (95% CI)
Health care utilisation (Received surgery for back or knee)			
Week 26	n/N (%)	n/N (%)	OR (95% CI)

a Intervention group of low back pain patients (trial one) only.

RMDQ=Roland Morris Disability Questionnaire; WOMAC=Western Ontario
and McMaster Universities Index; BMI=Body Mass Index; SF12.v2=Short
Form Health Survey version 2; PCS=Physical Component Score;
MCS=Mental Component Score; GPE=Global Perceived Effect;
DASS-21=Depression Anxiety Stress Scale; MVPA=Moderate-to-Vigorous
Physical Activity; AUDIT=Alcohol Use Disorders Identification Test;
SOPA=Survey of Pain Attitudes; FABQ=Fear Avoidance Beliefs
Questionnaire.

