#### Treatment allocation

Eligible patients were randomised in a 1:1 allocation ratio, to either
receive the weight management and healthy lifestyle intervention at that
time (intervention group) or remain as part of the cohort and be told they
will be offered clinical services in 6 months (control group). The
randomisation schedule was generated a priori by an independent statistician
using SAS 9.3 through the SURVEYSELECT procedure. To randomise patients, a
trained interviewer opened a sealed opaque envelope containing group
allocation. A staff member not involved in the study prepared the
envelopes.

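### The growth mixture model counts a group difference in the intercept, which is pre-randomisation pain if time runs from baseline, as one of three treatment effects per latent class

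*Protocol article*

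**What the plan says.** The Secondary analysis section first describes a hierarchical growth curve model with group, time and their interaction: "Between group differences in the trajectory of pain intensities over the" follow-up period. It then adds growth mixture models, with this purpose: "We will also investigate treatment effect heterogeneity that may exist" in latent subgroups. The random effects of that model are "effects that are all conditional trajectory class membership: intercept linear" slope and quadratic slope. On how group enters, the text says "The random effects are influenced by the treatment" group, "so there will potentially be 3 lots of treatment effects", one for each random effect, in each latent class.

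Three other places bear on what the intercept means:

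- Data collection and follow up says of baseline that the "assessment was conducted prior to randomisation".
- Primary outcome puts baseline first in the pain series: "These pain intensity scores were measured at baseline, at 2, 6, 10" and so on to week 26.
- Table 2 codes baseline as week 0. Table 3 lists Baseline to Week 26 under the secondary pain analysis and ends with a weekly trend.

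The article gives no other time origin, no centring, and no constraint on the intercept.

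**The concern.** If time is counted in weeks from baseline, the intercept of each trajectory is pain before allocation, and treatment cannot have changed it. The text nevertheless lists its group difference among the treatment effects of an analysis meant to find subgroups that respond differently. An arm difference in starting pain within one class could then be read as a subgroup-specific effect.

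Such a difference can arise in two ways. One is chance, which grows as the classes get smaller. The other is systematic. Classes are inferred from whole trajectories, which include post-randomisation pain. If treatment moves people between classes, the arms within a class need no longer be comparable at baseline, even though randomisation balanced them overall.

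**Working it through.** **The plan's count.** One intercept + one linear slope + one quadratic slope, each depending on group, gives 3 per class, so the stated figure reproduces. Without the intercept it is 2 per class. For 2, 3 or 4 classes the totals are 6, 9 or 12 with the intercept and 4, 6 or 8 without it.

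**Chance size of a within-class intercept difference.** The inputs come from the Sample size section: SD 2.3 and 80 per arm (trial one), SD 2.7 and 60 per arm (trial two). Allocation is 1:1 (Treatment allocation). The article gives no number or size of classes, so K equal classes are assumed. SE = SD × √(2 / (n/K)), and the 95% chance limits are ±1.96 × SE.

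| Trial | K | Per arm per class | SE | 95% limits (NRS points) | Design target |
|---|---|---|---|---|---|
| One | 2 | 40 | 2.3 × √(2/40) = 0.51 | ±1.01 | 1.5 |
| One | 3 | 26.7 | 2.3 × √(2/26.7) = 0.63 | ±1.23 | 1.5 |
| Two | 2 | 30 | 2.7 × √(2/30) = 0.70 | ±1.37 | 2 |
| Two | 3 | 20 | 2.7 × √(2/20) = 0.85 | ±1.67 | 2 |

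These use whole-sample SDs. Latent classes separate people by trajectory, so the within-class SD should be smaller and the figures are upper ones.

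**Chance of at least one false intercept effect.** With K independent tests this is 1 − (1 − α)^K. For K = 2, 3, 4 it is 9.8%, 14.3%, 18.6% at α = 0.05, and 2.0%, 3.0%, 3.9% at the 0.01 level that Analysis principles sets for secondary outcomes.

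**Systematic differences.** A simulation assumed 80 per arm, baseline SD 1.5, residual SD 1.5 and visits at weeks 0 to 26. People were split into two groups by late pain, as a stand-in for latent classes.

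- With no treatment effect, 9.6% of runs showed a nominal (0.05) intercept effect in at least one group, and the overall fitted intercept difference correlated 0.89 with the observed baseline difference.
- With a pure slope effect of −1.5 points over 26 weeks, the arms stayed balanced overall. In the low-pain group the intercept nevertheless differed by 0.38 points on average, and 34% of runs showed at least one nominal intercept effect.

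This shows the mechanism; it does not forecast what a fitted mixture model would give.

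**Would fixing the intercept difference at zero be better?** This was checked in a single-class linear growth model with 80 per arm. The assumed variance components are intercept SD 1.6, slope SD 0.06 per week, residual SD 1.5, and intercept–slope correlation −0.3, 0 or 0.3.

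| Quantity | Free intercept | Constrained (−0.3, 0, 0.3) |
|---|---|---|
| SE, week 26 difference | 0.334, 0.386, 0.432 | 0.309, 0.335, 0.348 (8%, 13%, 19% lower) |
| SE, weekly trend difference | 0.01345 | 0.01188, 0.01289, 0.01338 (12%, 4%, 0.5% lower) |
| Week 26 estimate if the true effect is −1.5 from week 2 on | −1.72 | −1.31, −1.10, −0.89 |

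In the last row the free linear model puts −0.95 of the effect into the intercept. A time form too stiff for an early change can therefore push a real effect into that term, and the constraint then makes the week 26 estimate worse.

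**The case against.** The strongest reply is that the article never states the time origin. If time were centred at a post-randomisation visit, the intercept difference could be a real treatment effect. A condensed article may also leave parameterisation to the full protocols it cites. This stands as a limit on the point: the reading rests on week-0 coding, the baseline row in Table 3 and a trend per week. It does not remove the point. The article itself calls the intercept contrast a treatment effect and gives no origin that would justify the label. Dropping baseline while still timing from randomisation would leave the intercept an extrapolation to time 0.

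A reader might infer more than the article supports in three respects.

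- **That the group, time and interaction growth curve model is also wrong.** It is a standard specification. Table 3 leaves the difference column empty for the visit rows and compares the arms only on the weekly trend, where the constraint gains about 0.5% to 12% in SE under assumed variance components.
- **That the intercept difference must be set to zero.** Randomisation balances the arms overall, not within classes informed by post-randomisation pain. With a poorly fitting time form the constraint can bias the week 26 difference.
- **That baseline imbalance will be published as heterogeneity.** Differences within the 95% limits are compatible with zero, and at the 0.01 level the chance of any false intercept effect is about 2% to 4% for two to four classes. That calculation covers chance only, not systematic within-class differences.

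**Conclusion.** The point holds as a mislabelled contrast in a secondary, exploratory analysis. Given time counted from baseline, one of the three stated effects per class is a pre-treatment difference and says nothing about treatment effect heterogeneity. Its possible size by chance, about 1.0 to 1.7 NRS points for two or three classes, is an upper range that assumes equal classes and whole-sample SDs. The primary AUC t-test and the other secondary outcomes are not touched. The consequence is modest, and correction is cheap.

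**What to change.** In the Secondary analysis section:

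1. State that time 0 is the baseline assessment.
2. Replace the count of three with treatment effects on the change terms only (linear and quadratic slope), and say that a group difference in the intercept will not be interpreted as a treatment effect.
3. Report the model-implied between-group difference at week 26 for each class.
4. Optionally, add a sensitivity analysis with the group effect on the intercept set to zero, using a time form flexible enough to follow an early change. The piecewise form the section already allows would do.

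Items 1 and 2 are wording. Item 3 is a contrast from the fitted model, and item 4 is one further fit. No new data are needed, and the growth curve model can stay as written.
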